### **18.3 Analysis of Efficacy – secondary endpoints**

The mRS score will be used to evaluate the proportion of patients with a score = 0 to 4 *versus* 5 or 6, 0 to 3 *versus* 4 or higher, 0 to 2 *versus* 3 or higher, 0 to 1 (or return to pre stroke morbidity) *versus* 2 or higher and at day 90 $\pm$ 7. The adjusted risk ratio will be calculated by fitting the GLM models separately.

NIHSS score at 5-7 days or at early discharge and Functional health status quality of life 90 ( $\pm$ 7) days after randomization (EQ-5D-VAS). The EQ-5D-VAS will be compared between the methylprednisolone group and the placebo group via GLM.

Normality and variance homogeneity of residuals will be accessed graphically. The win ratio method will be used if normality assumption is seriously violated.

The significance of each test is determined at the two-sided alpha level of 0.05. The specific statistical model for analysing each of these outcome measures will be detailed in the Statistical Analysis Plan (SAP).

### **18.4 Safety analysis**

Safety outcomes include incidence of overall mortality at 90 ( $\pm$ 7) days after randomization, the proportion of patient with SICH within 48 hours after treatment, the proportion of patient with any ICH within 48 hours after treatment, proportion of patients with pneumonia and proportion of patients with gastrointestinal haemorrhage within 7 days after EVT;. The safety analysis will be performed on the Safety

Population. The incidences of each outcome will be compared via Chi-square test or Fisher's exact test. The modified Poisson regression models will be fitted to estimate the risk-ratio associated with the treatment effect. Risk ratio with 95% CI will be reported. Patients with missing outcome will not be included in the regression analysis. Additionally, Log-Rank test and the Kaplan-Meier estimates will be plotted over the observation period of 90 days for mortality. Cox regression model will be employed to calculate the hazard ratio with 95%CI.

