### **18.1 Determination of sample size**

The current trial is designed detect a shift on the modified Rankin Scale score, which represents the global disability, to a lower score. The expected distribution of the modified Rankin Scale score, derived from the EVT for acute anterior circulation ischemic stroke (ACTUAL) registry and the Highly Effective Reperfusion evaluated in Multiple Endovascular Stroke Trials (HERMES) collaboration, is as follows: 7%, 20%, 16%, 11%, 13%, 8% and 25%.

The sample size was calculated using the cumulative proportion of patients with mRS 0-2. We assume a moderate effect of 7% absolute increase in the cumulative proportion of patients with mRS 0-2 in the intervention group, compared with controls, indicating an odds ratio (OR) of 1.33, which have substantially exceeds the minimal clinically important difference. In order to demonstrate the expected treatment effect with a type-1 error  $\alpha=0.05$  (two-tailed) and a power of 80% ( $\beta=20\%$ ). A sample size of  $n=1588$  patients ( $n=794$  per treatment group) is required.

The intention-to-treat principle will be applied to the primary analysis and, therefore, to safeguard against dilution of the treatment effect associated with an approximate 5% non-adherence rate (due to loss to follow-up, consent withdrawal and other reasons), we initially planned to enrol  $n=1672$  patients ( $n=836$  per treatment group) for this study. This estimation was performed based on PASS (NCSS, LLC, Kaysville, Utah, USA) version 15.0.

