### **18.6 Adjustment for Covariates and Subgroup Analyses**

In addition to the primary and secondary analyses adjusting for age, baseline NIHSS score, pre-stroke mRS, baseline ASPECTS score, the use of intravenous thrombolysis, time from onset to randomization, and occlusion location, exploratory analyses will be conducted to determine the potential roles of common baseline characteristics and assess potential heterogeneity of treatment effect across subgroups. The primary pre-specified subgroups as follows will be explored.

- age
- sex
- baseline NIHSS score
- pre-stroke mRS
- baseline ASPECTS score
- intravenous thrombolysis

- time from last known well to randomization. (mins)
- occlusion location
- Complete Reperfusion defined as Extended Thrombolysis in Cerebral Infarction grade 2c or 3
- Patients with any radiological haemorrhages
- Patients with symptomatic haemorrhages

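### Section 18.4 gives 90-day mortality only unadjusted tests and names no covariates for its regression models, while the day-90 mRS analyses adjust for seven; name one main, covariate-adjusted mortality analysis

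*Supplement*

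**What the plan says.** All references are to protocol version 2.0.

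- **Mortality.** Section 15.3.1 lists two primary safety endpoints: all-cause mortality at 90 days and symptomatic intracranial haemorrhage within 48 hours. Section 18.4 compares the incidence of each safety outcome by chi-square or Fisher's exact test, then states: "The modified Poisson regression models will be fitted to estimate the risk-ratio associated with the treatment effect". For mortality it adds log-rank, Kaplan-Meier and a Cox hazard ratio. No covariate is named for any of these.
- **Synopsis.** Under Statistical Methods, modified Poisson regression is itself the test for mortality, again without covariates.
- **Efficacy.** Section 18.2 (primary endpoint) adjusts for age, baseline NIHSS, pre-stroke mRS, ASPECTS, intravenous thrombolysis, time from onset to randomization and occlusion location. For the four mRS dichotomies, section 18.3 says: "The adjusted risk ratio will be calculated by fitting the GLM models separately".
- **General statement.** Section 18.6 opens: "In addition to the primary and secondary analyses adjusting for age, baseline NIHSS", and continues with the same seven variables. It does not say whether the safety endpoints are among those analyses.

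**The concern.** Death is grade 6 of the primary scale (section 15.1), so the plan already treats these seven variables as worth adjusting for on the same day-90 scale. If mortality is analysed without them, the harm question is answered less precisely than the benefit question from the same follow-up. Randomization is stratified by centre only (section 11), so a chance imbalance in age or stroke severity would move the unadjusted mortality ratio.

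There is a clarity problem as well. A reader cannot tell which of chi-square or Fisher, modified Poisson, log-rank or Cox is the main mortality result, or whether the two regressions carry covariates. With several candidate analyses and no stated order, the choice can be made after the data are seen.

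**Working it through.** **Inputs from the plan (section 18.1).** The expected mRS distribution "is as follows: 7%, 20%, 16%, 11%, 13%, 8% and 25"% gives mRS 0-2 = 7 + 20 + 16 = 43% and death = 25%. The design effect is described thus: "We assume a moderate effect of 7% absolute increase in the cumulative proportion of patients with mRS 0-2 in the intervention group". Alpha is 0.05 two-sided, power 80%, and 794 per group are required.

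**The plan's own figure.** With 43% against 50% and unpooled variance:

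n = (1.960 + 0.842)² × (0.43×0.57 + 0.50×0.50) / 0.07² = 793.1, so 794 per group and 1588 in total.

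The odds ratio is (0.50/0.50)/(0.43/0.57) = 1.326, and 1588/0.95 = 1671.6, so 1672. The plan's figures reproduce, which supports reading the distribution as that of the control arm.

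**Assumptions not in the plan.** The plan states no power for mortality, no harm effect and no prognostic strength. I assume 30% or 31% mortality on drug, and an R² (share of the variance in death explained by the covariates) of 0.08 to 0.25.

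**Formula.** Power = Φ(|p1 − p0|/SE − 1.96), with SE² = [p0(1−p0) + p1(1−p1)]/794 × (1 − R²).

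Unadjusted, 25% against 30%: SE = √[(0.1875 + 0.2100)/794] = 0.02237; 0.05/0.02237 − 1.96 = 0.275; power 60.8%.

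Unadjusted, 25% against 31%: SE = √[(0.1875 + 0.2139)/794] = 0.02248; 0.06/0.02248 − 1.96 = 0.709; power 76.1%.

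| Assumed R² | SE multiplier √(1−R²) | Power, 25% vs 30% | Power, 25% vs 31% |
|---|---|---|---|
| 0 | 1.000 | 60.8% | 76.1% |
| 0.08 | 0.959 | 64.4% | 79.5% |
| 0.10 | 0.949 | 65.4% | 80.3% |
| 0.15 | 0.922 | 67.9% | 82.5% |
| 0.20 | 0.894 | 70.5% | 84.7% |
| 0.25 | 0.866 | 73.2% | 86.9% |

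The gain is about 4 to 12 points for the 5-point increase and 3 to 11 points for the 6-point increase.

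**Simulation check.** Modified Poisson with robust variance was fitted to 1500 simulated trials per scenario, with 794 per arm, a logistic outcome and one combined prognostic score. At 25% against 31%:

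| R² (AUC of score) | Power unadjusted | Power adjusted | SE of log risk ratio |
|---|---|---|---|
| 0.08 (0.68) | 75.9% | 78.7% | 0.0812 → 0.0778 |
| 0.15 (0.74) | 74.8% | 81.8% | 0.0812 → 0.0754 |
| 0.24 (0.81) | 75.4% | 85.0% | 0.0813 → 0.0728 |

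The standard error falls by 4%, 7% and 10%, a little less than √(1−R²) implies, so the formula is mildly optimistic at high R². With equal mortality in both arms, both analyses rejected in 4 to 6% of trials.

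**Detectable increase at 80% power** (pooled formula, 794 per arm): 6.3 points unadjusted; 6.1, 5.8 and 5.5 points at R² 0.08, 0.15 and 0.24.

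**The case against.** The strongest objection is that the absence of covariates is inferred from silence. The protocol elsewhere omits the word where adjustment is intended: the synopsis reports plain risk ratios for the mRS dichotomies that 18.3 calls adjusted. Section 18.6 speaks of primary and secondary analyses without limiting them to efficacy, and section 15.3 itself sorts safety endpoints into primary and secondary. Model covariates are commonly set in the SAP. All of this stands. A reader might infer that the mortality risk ratio and hazard ratio are definitely unadjusted; the text does not establish that.

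Three things remain. Chi-square, Fisher and log-rank, as written, are unadjusted whatever the SAP says. Section 18.4 has no pointer to the SAP, whereas 18.2 (primary endpoint), 18.3 and 18.7 do. And the synopsis and 18.4 differ on the mortality test.

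A second objection is that an unadjusted comparison in a 1:1 randomized trial is valid, with chance imbalance already reflected in the confidence interval. That is right. A reader might infer bias or an inflated error rate; neither follows, and the simulation shows no type I error problem. Nor should much be made of possible disagreement between mRS 0-4 and mortality: mRS 5-6 includes survivors, and the ITT and Safety Populations differ in how patients are classified.

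A third is that adjustment can change what is estimated. For the risk ratio from a log-link model with randomized treatment and no interaction terms, it does not. For the Cox hazard ratio it does, because the hazard ratio is not collapsible; the precision argument therefore does not carry over to it.

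**Conclusion.** The point holds as one of efficiency and pre-specification, not as an error that invalidates the analysis. For one of its two primary safety endpoints, the plan leaves the main analysis open and relies on unadjusted tests, although it uses seven suitable baseline covariates elsewhere. The cost is modest: a standard error of the log risk ratio about 4 to 10% lower with adjustment in simulation (R² 0.08 to 0.24), and by formula about 3 to 12 points of power against an assumed 5 to 6 point increase in deaths. The size rests on the plan's 25% mortality applying to the control arm, 794 evaluable patients per arm, and the assumed harm effect and R². If the SAP already specifies an adjusted mortality risk ratio as the main result, only the wording of 18.4 and the synopsis needs aligning.

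**What to change.** In 18.4, and in matching words in the synopsis and SAP, state that the main mortality analysis is the modified Poisson risk ratio with robust standard errors, adjusted for the same seven baseline covariates as the primary efficacy model. Keep the unadjusted proportions, chi-square test, Kaplan-Meier curves with log-rank, and unadjusted Cox hazard ratio as supporting results. If an adjusted hazard ratio is also reported, label it conditional and show it beside the unadjusted one.

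The cost is a sentence or two. The covariates are already needed for the efficacy models, and section 18.7 provides for imputing missing values. The small downside is that the main mortality estimate would then depend on a regression model and on some imputed covariates, which the supporting unadjusted results let a reader check.

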|  | 
compared between two randomized treatment groups using GLM. The mean difference and corresponding 95%CI will be provided. Normality and variance homogeneity of residuals will be accessed graphically. The win ratio method will be used if normality assumption is seriously violated.
 
Analysis of Safety:
 
The safety analysis will be conducted on the Safety Population.
 
Mortality due to any cause at <math>90 \pm 7</math> days. The difference of mortality in two treatment groups will be tested using modified Poisson Regression. In addition, the Kaplan-Meier method will be used to assess the mortality. The log-rank test will be applied to compare the two treatment groups. Cox regression model will be employed to calculate the hazard ratio with 95%CI.
 
In addition to mortality due at <math>90 \pm 7</math> days, SICH within 48 hours is considered to be another primary safety outcome. SICH will be evaluated according to the modified Heidelberg Bleeding Classification. Besides, modified Poisson regression will be fitted to estimate the risk ratio associated with the treatment effect. The proportion of Any radiologic ICH within 48 hours between methylprednisolone and placebo groups will be tested in the same manner as SICH.
 
Proportion of patients with pneumonia and proportion of
 |

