## **15.3 Safety Analysis-Primary Endpoint**

### **15.3.1 Primary Safety Endpoints**

- Mortality due to any cause at 90 (±7) days;
- Proportion of patients with symptomatic intracranial haemorrhage within 48 hours after endovascular treatment. Symptomatic intracranial haemorrhage will be adjudicated by an independent Imaging Core Laboratory and the Clinical Events Committee according to the modified Heidelberg Bleeding Classification, and is diagnosed based on a combination of: 1) clinical deterioration, 2) imaging findings, and 3) causal relatedness assessment. Clinical deterioration is defined as any of the following conditions: 1) NIHSS score increased more than 4 points than that

immediately before worsening; 2) NIHSS score increased more than 2 points in one category; 3) Deterioration led to intubation, hemicraniectomy, external ventricular drain placement or any other major interventions. The imaging criteria are presence of parenchymal hematoma type 2 (PH2), parenchymal hematoma type 1 (PH1), remote intracerebral haemorrhage (RIH), subarachnoid haemorrhage (SAH), intraventricular haemorrhage (IVH), or subdural haemorrhage. When clinical deterioration and PH2 co-occur, the event is automatically categorized as SICH. When clinical deterioration and PH1/RIH/SAH/IVH/SDH co-occur, the event is deemed SICH if it is judged that the haemorrhage contributed substantially to the clinical worsening. When clinical deterioration occurs only with haemorrhagic infarction type 1 or 2 (HI1 or HI2), the event is automatically classified as not SICH. ICH.

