## **16.2 Assessment of safety**

### **16.2.1 Mortality at 90±7 days**

Mortality at 90±7 days is one of the most important safety endpoints of the MARVEL trial. Mortality rates are defined as the number of deaths observed divided by the number of subjects observed over the 90-day study period.

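### Section 18.4 estimates the 90-day mortality risk ratio on complete cases only and names no sensitivity analysis for it, although the time-to-event methods planned beside it can use partial follow-up

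*Supplement*

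**What the plan says.** All references are to protocol version 2.0.

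- Section 15.3.1 lists all-cause death at 90 (±7) days as a primary safety endpoint.
- The synopsis names the test: "The difference of mortality in two treatment groups will be tested using modified Poisson Regression". It then adds that "the Kaplan-Meier method will be used to assess the mortality", with log-rank and Cox.
- Section 18.4 compares incidences by chi-square or Fisher's exact test and fits modified Poisson models for risk ratios. It continues: "Patients with missing outcome will not be included in the regression analysis". After that sentence come "Additionally, Log-Rank test and the Kaplan-Meier estimates will be plotted over the observation period of 90 days for mortality" and "Cox regression model will be employed to calculate the hazard ratio with 95%CI".
- Section 16.2.1 defines the rate: "Mortality rates are defined as the number of deaths observed divided by the number of subjects observed over the 90-day study period". It does not say how a patient followed for part of the 90 days is counted.
- Section 18.7 promises sensitivity analyses on missingness for the primary outcome, which is the mRS. It names none for mortality.

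**The concern.** For most binary outcomes, complete-case analysis treats patients with and without the outcome symmetrically. For death it does not. A death seen during follow-up is a known outcome and is always counted, whereas a patient can become missing only while alive. Excluding the missing therefore removes people known to have survived for some time and removes no observed death. Kaplan-Meier and Cox methods can use that survival time, so two sets of results for one primary safety endpoint may rest on different patients.

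At stake are the reported 90-day rate in each arm, the risk ratio if loss differs between arms, and how to read a risk ratio and a hazard ratio that disagree only because of who was counted.

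**Working it through.** **Inputs from the protocol.** Expected deaths are 25% (the mRS 6 share in section 18.1), with 836 patients per arm. The only figure bearing on loss is the sample-size allowance, an "approximate 5% non-adherence rate (due to loss to follow-up, consent withdrawal and other reasons". The protocol gives no mortality power, missingness or bias figure.

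**The plan's own sample size reproduces.** For mRS 0-2 at 43% vs 50%, two-sided 0.05 and 80% power, unpooled variance: (0.43×0.57 + 0.50×0.50) × (1.960 + 0.842)² / 0.07² gives 794 per arm after rounding up. Then 794 / 0.95 = 835.8, so 836.

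**Assumptions.** A share L of each arm has no day-90 status. A share f of the arm's 90-day deaths occurs before the time of loss. Censoring is independent. The protocol gives neither the timing of deaths nor a forecast of unknown vital status, so f and L are shown over ranges.

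**Formulas.**
- Residual risk of a patient lost alive: r = (0.25 − 0.25f) / (1 − 0.25f)
- Complete-case rate: (0.25 − L·r) / (1 − L)
- SE of one arm's rate: √(0.25×0.75/836) = 0.0150, or 1.5 points

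**Bias in the rate, L = 5%:**

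| f | r | Complete-case rate | Bias (points) | Bias / SE |
|---|---|---|---|---|
| 0.2 | 0.2105 | 25.2% | +0.2 | 0.14 |
| 0.4 | 0.1667 | 25.4% | +0.4 | 0.3 |
| 0.6 | 0.1176 | 25.7% | +0.7 | 0.5 |
| 0.8 | 0.0625 | 26.0% | +1.0 | 0.7 |
| 1.0 | 0 | 26.3% | +1.3 | 0.9 |

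The visit schedule bears on f. After the treatment-period visit at 48-96 h, scheduled contacts are day 5-7 (or earlier discharge) and day 90 ± 7. Someone who misses the last visit was usually last seen in about the first week, which makes f = 0.2 to 0.4 plausible. Late loss is also possible: section 17.1 counts unwillingness to attend the 3-month assessment as a ground for withdrawal.

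**Less loss.** At L = 2% the bias is at most 0.25/0.98 − 0.25 = +0.5 points.

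**Simulation check** (2 million patients, true mortality 25%, about 5% lost, independent censoring, loss spread over follow-up or placed at day 90): complete-case 25.6% to 26.3%, Kaplan-Meier 25.0%.

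**If censoring is not independent.** For mortality d among the lost, the bias is L(0.25 − d)/(1 − L). At L = 5% this is +1.32 points for d = 0, +0.79 for d = 10%, 0 for d = 25%, −0.79 for d = 40% and −1.84 for d = 60%.

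**Risk ratio.**
- Equal loss and equal prognosis: both arms' rates are inflated by the same factor, which cancels.
- Equal 5% loss, illustrative true ratio 0.80 (25% vs 20%): 0.80 if no lost patient died, 0.796 if 10% of the lost died in each arm, 0.778 if 50% did.
- Loss of 7% vs 3% with no true effect: at f = 0.6, 0.2600/0.2541 = 1.02; at f = 1, 0.97/0.93 = 1.04. At f = 0.4 it is 1.015.
- SE of the log risk ratio: √(2×0.75/0.25/836) = 0.085. ln 1.043 = 0.042, so the largest of these shifts is 0.5 SE.

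**Bounds for one arm** with 209 deaths seen and 42 of 836 unknown: complete case 209/794 = 26.3%; all unknown alive 209/836 = 25.0%; all unknown dead 251/836 = 30.0%.

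**The case against.** Three stronger readings are tempting, and the documents do not support them.

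1. *The reported rate is biased upward.* The quoted rule governs a regression that yields a risk ratio. For the rate, the sign depends on mortality among the lost. It is upward under independent censoring, zero if the lost die at the overall rate, and downward if they die more often.
2. *The protocol sets two explicit follow-up rules and two denominators.* No censoring rule is written, so following patients to last contact is only the usual convention for Kaplan-Meier and Cox. Section 16.2.1 does not say that partly followed patients leave the denominator. The SAP is not in the supplement and may hold the censoring rule, so its absence from the protocol is not counted as a fault here.
3. *The treatment comparison is compromised.* The trial is double-blind and placebo-controlled, and nothing suggests unequal loss. The 7% vs 3% split is illustrative, and even that moves the ratio by at most half a standard error.

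Some further points on the other side also stand. The 5% covers every reason for non-adherence and does not forecast unknown vital status. Section 17.2 follows patients who stop treatment to day 90, and section 17.1 asks for every effort to obtain information on those who withdraw. Unknown vital status is also a missing mRS, so the planned mRS sensitivity analyses touch it indirectly. A risk ratio supplemented by time-to-event analyses is ordinary practice.

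These points limit the size and certainty of the bias. They do not remove the written exclusion: section 18.4 states it outright for the model that tests a primary safety endpoint and, unlike sections 18.2, 18.3 and 18.7, does not refer to the SAP.

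**Conclusion.** The point holds in a limited form. The stated test of 90-day mortality uses complete cases only. Methods planned alongside it can use partial follow-up, and the protocol names no sensitivity analysis for mortality.

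Under independent censoring, with 25% deaths and 5% of status unknown, the complete-case rate is too high by about 0.2 to 0.4 points in the case that best fits the visit schedule, and by 1.3 points at most. This rests on the assumed timing of loss and on treating the whole 5% allowance as unknown status. Informative loss could reverse the sign. The risk ratio is close to unbiased with similar loss and prognosis in the two arms, and shifts to about 1.02-1.04 under a 7% vs 3% split with no true effect and 60-100% of deaths before loss.

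The bias is small, but it is avoidable at almost no cost in a primary safety endpoint.

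**What to change.** In sections 16.2.1 and 18.4, for mortality only:

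- Replace the exclusion of patients with missing outcome by day-90 Kaplan-Meier risks in the Safety Population, censored at the date last known alive. Report the risk ratio with 95% CI from the two estimates, or from a modified Poisson model weighted for censoring.
- Keep the complete-case modified Poisson risk ratio as a sensitivity analysis.
- Add best-case and worst-case bounds for patients whose day-90 vital status is unknown.
- Carry the same wording into the synopsis.

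The cost is wording, plus a recorded date last known alive for each patient. The Kaplan-Meier curves are already planned. The one drawback is that Kaplan-Meier assumes uninformative censoring; the bounds show how far the result could move if that fails.
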